### Vital sign, physical exams and other assessments

The following physical examination, vital signs, cardiac examinations will be performed/measured as described in the flowchart:

Vital signs including heart rate, blood pressure (systolic/diastolic blood pressure, supine), respiratory rate and body temperature ( $^{\circ}\text{C}$ );

12-lead ECG. This examination can be repeated in case of occurrence of an adverse event;

The physical examination always comprises the following body systems: cardiovascular, central nervous system, respiratory system.

Clinically significant abnormalities of physical examinations, vital signs, ECG, echocardiogram examinations must be recorded as an adverse event on the appropriate section of the eCRF.

All ECGs as part of standard of care or for assessment of a possible AE outside of the scheduled visits will be collected as unscheduled assessments.

### 7.13.2 Pharmacokinetics, soluble GPVI and Immunogenicity Assessments

It is of utmost importance to collect all blood samples at the specified times and according to the specifications.

Samples missed or lost, for any reason, should be recorded. Actual date and times of blood collection must be recorded in the eCRF. The date and the time of drug administration should also be precisely recorded.

PK will be assessed and sampling times for blood collection can be found in the study flow chart (see [Section 7.1](#)).

Plasma samples for PK, soluble GPVI and immunogenicity assessments will be analyzed by a Central Laboratory and those samples should be transferred according to the detailed procedure described in the Central laboratory instruction manual.

| Visit                    | Time                                 | Sample nr
PK | Sample nr
ADA | Sample nr
sGPVI |
|--------------------------|--------------------------------------|-----------------|------------------|--------------------|
| Visit 2 Day 2 (V2D2)     | Baseline                             | 201             | 211              | 221                |
|                          | 3hrs after start of infusion         | 202             |                  |                    |
|                          | 3hrs after end of infusion           | 203             |                  |                    |
| Visit 3 Day 3 (V3D3)     | 24hrs after 1 st infusion | 301             |                  |                    |
|                          | 3hrs after start of infusion         | 302             |                  |                    |
|                          | 3hrs after end of infusion           | 303             |                  |                    |
| Visit 4 Day 4 (V4D4)     | 24hrs after 2 nd infusion | 401             |                  |                    |
|                          | 3hrs after start of infusion         | 402             |                  |                    |
|                          | 3hrs after end of infusion           | 403             |                  |                    |
| Visit 5 Day 5 (V5D5)     | 24hrs after 3 rd infusion | 501             |                  |                    |
|                          | 96hrs evaluation                     |                 |                  | 521                |
| Visit 10 Day 40 (V10D40) | EOS                                  |                 | 1011             |                    |

Table 1: laboratory assessment and sample numbers

PK analyses will be done at QPS (see [Section 9.4.1](#)).

Potential presence of ADA will be determined at QPS in all patients enrolled and sampling times for blood collection can be found in the study flow chart (see [Section 7.1](#)). In case the patient presents clinical symptoms suggesting the potential presence of ADA, a blood sample may be collected outside of the scheduled visits as unscheduled ADA assessment see [Section 9.4.2](#)).

Sample handling, storage, and shipping conditions will be described in a specific manual intended for the investigating team.

QPS should be provided in due time and with a procedure that complies with blinding conditions with the list of tubes (both for PK and ADA) that stem from patients having received the active IMP.

To avoid any unintended unblinding, all the results related to PK and ADA won't be shared with either the sites staff, the Sponsor nor the CRO staff involved in the study management before the database lock.

## 8. PRIMARY ENDPOINT

### 8.1 EFFICACY

#### 8.1.1 Primary Efficacy Endpoint : Progression from moderate to severe respiratory distress assessed at Day 4

The primary efficacy endpoint is a composite failure endpoint defined as the occurrence of at least one of the following failure events at Day 4 :

- $RR \geq 30/\text{min}$ , or/and
- $SpO_2$  decrease  $> 5\%$  in ambient air. In case where oxygenotherapy cannot be discontinued, please refer to NEWS 2 Scale (item  $SpO_2$ , scale 2) for adequate conversion (e.g. 93-94 on  $O_2$  corresponding to 86-87 in ambient air),  $PaO_2/FiO_2 \leq 100\text{mmHg}$  or/and
- Death occurring prior to or on Day 4

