### 5.1.2 Non-Inclusion Criteria

1. Patients requiring invasive/assisted mechanical ventilation (intubation),
2. Obvious disseminated intravascular coagulation (DIC), (with e.g. a variable combination of the following: low platelet count ( $< 100,000/\text{mL}$ ), prolonged PT  $> 12\text{sec}$  and/or aPTT  $> 60\text{sec}$ , presence of fibrin degradation products in the plasma, with or without clinically visible hemorrhagic signs). An isolated change of one of these parameters does not qualify for DIC,
3. ARDS of another origin,

4. Concomitant pulmonary infection (pneumoniae) with another agent, notably bacterial or fungal,
5. Patients presenting with hemoglobin < 9g/dL,
6. Patients under immunosuppressive agents,
7. Patients receiving an anti-cancer treatment (radiotherapy, chemotherapy, immunotherapy)
8. Initiation of a treatment with aspirine (previous stable preventative aspirin regimen from 75 to 160 mg per day is allowed),
9. Patients under anticoagulant therapy (except heparin and low-molecular weight heparin), and anti-Xa drugs achieving effective anticoagulation, as assessed by appropriate tests, or having received thrombolytics  $\leq 24$  hrs,
10. Patients receiving NSAIDs or anti-platelet agents with platelet suppression within the past 7 days,
11. Patients treated concomitantly with another monoclonal antibody (e.g. tocilizumab),
12. Ischemic stroke or transient ischemic attack within the past year,
13. Deep venous thrombosis or pulmonary embolism within the past year,

14. Severe renal insufficiency (Grades 4-5) with a glomerular filtration rate  $<30\text{mL/Min}/1.73\text{m}^2$ ,
15. One of the following severe organ failures:
  - Hepatic with either Child Pugh score  $\geq\text{C}$ , or ASAT/ALAT  $\geq 5$  U.N.L,
  - Cardiac with NYHA  $\geq$  Class II, unstable angina pectoris, myocardial infarct  $<1$  year, supra-ventricular or ventricular arrhythmia,
16. Hereditary tendency to bleeding or coagulopathy,
17. Severe vascular disease (aneurysms, arterial surgery  $\leq 6$  months),
18. Unhealed wounds, gastrointestinal ulcers or perforation  $\leq 6$  months,
19. Major surgery  $<28$  days, other surgery within the past 7 days,
20. Hemoptysis, GI bleeding, CNS bleeding  $<1$  month,
21. Platelet count  $<50,000/\text{mm}^3$  (50 g/L),
22. Absolute Neutrophil Count  $\leq 1,000/\text{mm}^3$  (1.0 g/L),
23. Terminal illness, including cancer (life expectancy  $<3$  months),

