## 9. SECONDARY ENDPOINTS

### 9.1 EFFICACY

- All cause Death at day 40 and Overall Survival
- WHO-COVID-19 Scale
- NEWS-2 Scale
- Respiratory Rate status defined as::
  - Normal:  $< 20/\text{min}$ ,
  - Mild:  $20 \leq RR < 24/\text{min}$ ,
  - Moderate:  $24 \leq RR < 30/\text{min}$ ,
  - Severe:  $\geq 30/\text{min}$ ,
  - Death.
- Hypoxemia status defined as::
  - Normal:  $> 300 \text{ mmHg}$ ,
  - Mild:  $200 \text{ mmHg} < PaO_2/FiO_2 \leq 300 \text{ mmHg}$ ,
  - Moderate:  $100 \text{ mmHg} < PaO_2/FiO_2 \leq 200\text{mmHg}$ ,
  - Severe:  $PaO_2/FiO_2 \leq 100\text{mmHg}$ ,
  - Death.
- $SpO_2$  status defined as:
  - Normal:  $> 95\%$
  - Mild:  $93 < SpO_2 \leq 95\%$ ,
  - Moderate:  $90 < SpO_2 \leq 93\%$ ,
  - Severe:  $\leq 90\%$ ,
  - Death.
- Chest CT-Scan (or in exceptional cases, chest radiogram)
- Oxygen-free days (over the study period = 40 days),
- Need for mechanical ventilation,

- Mechanical ventilation-free days,
- Hospital-free days (over study period = 40 days),
- Clinical Recovery and Time to Clinical recovery (over study period = 40 days),
- Cure and Time-to-cure (over study period = 40 days).

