#### **Primary efficacy endpoint: Progression from moderate to severe respiratory distress assessed at Day 4**

Progression from moderate to severe respiratory distress assessed at Day 4 is a composite failure endpoint defined as the occurrence of at least one of the following failure events at Day 4 :

- $RR \geq 30/\text{min}$ , or
- $SpO_2$  decrease  $> 5\%$  in ambient air. In case where oxygenotherapy cannot be discontinued, please refer to NEWS 2 Scale (item  $SpO_2$ , scale 2) for adequate conversion (e.g. 93-94 on  $O_2$  corresponding to 86-87 in ambient air),
- $PaO_2/FiO_2 \leq 100\text{mmHg}$
- Death occurring prior to or on Day 4

The composite event rate will be estimated within each group. The difference in composite event rates and the odds ratio will be estimated along with their asymptotic and exact 95% confidence intervals. p-values from the chi-square and exact Fisher test will also be provided.

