#### **Handling missing data:**

When the composite endpoint contains missing components, the composite endpoint is a failure if at least one non missing component is a failure. If all non missing components are successes, the composite endpoint is not computable and missing components should be imputed. In that latter case, a procedure for imputing missing components depending on the status of the last available component value (failure or success) will be proposed and detailed in the SAP.

**Component-wise secondary analysis:** an analysis of each individual binary component will be performed as an aid to the interpretation of the overall result of the composite. The difference in component event rates and the odds ratio will be estimated along with their asymptotic and exact 95% confidence intervals. p-values from the chi-square and exact Fisher test will also be provided. No adjustment for multiplicity will be used.

Multi-component analysis: an additional secondary analysis will be performed to assess the proportion of patients with one failure only, 2 failures and 3 failures among the 3 components (except death).

Sensitivity analyses will be proposed and detailed in the SAP.

Additional analyses of the primary endpoint: the primary composite endpoint will be analyzed in a logistic regression model including treatment effect and relevant covariates ( e.g. baseline WHO-Covid-19 scale) that will be specified in the SAP.

Subgroup analyses:

If feasible (i.e. when subgroup sizes are sufficient), subgroup analyses of the primary endpoint will be performed by BMI ( <30 vs >=30 ), Age (< 60 vs >=60) , by baseline WHO-Covid-19 scale , comorbidity, concomitant medications will be provided and further detailed in the SAP.

The same analysis proposed for the primary efficacy endpoint assessed at day 4 will be provided at other time points (Days 1, 2, 3, 7, 14, 20 and 40). The primary endpoint and its components will also be described via plots (e.g., stacked bar plots representing the proportion of subjects in each category (failure or not) , by treatment arm, over time).

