|                                               | Intubation and mechanical ventilation                        | 6            |
|                                               | Ventilation + additional organ support – pressors, RRT, ECMO | 7            |
| Dead                            | Death                                                        | 8            |

*Appendix 3 : Conversion tables for estimation of PaO2 and FiO2*[figure not shown]**Instructions to complete the CRFs****Conversion tables****1 Estimating PaO2 from a given SO2**

| SO 2 (%) | PaO 2 (mmHg) |
|---------------------|-------------------------|
| 80                  | 44                      |
| 81                  | 45                      |
| 82                  | 46                      |
| 83                  | 47                      |
| 84                  | 49                      |
| 85                  | 50                      |
| 86                  | 52                      |
| 87                  | 53                      |
| 88                  | 55                      |
| 89                  | 57                      |
| 90                  | 60                      |
| 91                  | 62                      |
| 92                  | 65                      |
| 93                  | 69                      |
| 94                  | 73                      |
| 95                  | 79                      |
| 96                  | 86                      |
| 97                  | 96                      |
| 98                  | 112                     |
| 99                  | 145                     |

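### The primary composite has no ventilation component and reads its three physiological thresholds at Day 4, so a patient intubated before the 96-hour assessment may be scored as not progressed

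*Protocol*

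**What the plan says.** Section 8.1.1 calls the primary endpoint a "composite failure endpoint defined as the occurrence of at least one of the following failure events at Day 4", and Section 11.5.1 repeats the timing. The events are a respiratory rate of 30/min or more, an SpO2 fall of more than 5% in ambient air (with a conversion when oxygen cannot be stopped), PaO2/FiO2 of 100 mmHg or less, and "Death occurring prior to or on Day 4". Death is the only event that is explicitly carried forward from an earlier day. The multi-component analysis in Section 11.5.1 counts "one failure only, 2 failures and 3 failures among the 3 components (except death"), which confirms that nothing else belongs to the composite. Section 7.7 places the recording at the Day 4 visit.

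Ventilation appears in three other places:

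- Section 5.1.2 excludes "Patients requiring invasive/assisted mechanical ventilation (intubation").
- Section 9.1 lists "Need for mechanical ventilation" and ventilation-free days as secondary endpoints.
- Appendix 2 has "Intubation and mechanical ventilation" as WHO score 6, under severe hospitalised disease.

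For missing components, Section 11.5.1 scores failure if any observed component fails. Otherwise it foresees "imputing missing components depending on the status of the last available component value (failure or success"), with the procedure left to the SAP.

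The synopsis (Efficacy Endpoints and Statistical Methods) says that progression is assessed at Day 4, but its sentence on the failure events does not repeat that time point.

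**The concern.** The primary objective is to prevent clinical progression, and the endpoint is titled as progression from moderate to severe respiratory distress. Because patients needing intubation cannot enter, an intubation by Day 4 is new after inclusion and is severe on the protocol's own ordinal scale. The components of the primary endpoint, however, are quantities that the ventilator controls or supports: the machine governs the rate, saturation is maintained, and ambient-air SpO2 cannot be measured.

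A patient can thus be severe on Appendix 2 and a non-failure on the primary endpoint at the same visit. The arm with more such patients would look better than it is. The study's stated aim is to estimate the treatment difference so that later trials can be designed (Section 11.4), so a distortion of that estimate bears directly on its purpose.

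**Working it through.** **The plan's own figure.** Section 11.4 states at least 80% power with 30 per arm for death rates of 0.40 v 0.10 and 0.30 v 0.04. With the unpooled Z test, power = Φ(|p1 − p2| / √(p1q1/30 + p2q2/30) − 1.96):

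- 0.40 v 0.10: Φ(0.30/0.1049 − 1.96) = 81.6%
- 0.30 v 0.04: Φ(0.26/0.0910 − 1.96) = 81.5%

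The statement reproduces, but it concerns death and not the composite. It neither supports nor weakens this point.

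**Can a ventilated patient pass every component?** The inputs are the thresholds in Section 8.1.1 and the SO2-to-PaO2 table in Appendix 3. FiO2 values and the ventilator-set rate are assumed. The ratio is PaO2/FiO2.

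| FiO2 | SO2 | PaO2 | Ratio | Component |
|---|---|---|---|---|
| 60% | 93% | 69 | 69/0.60 = 115 | not failed |
| 70% | 93% | 69 | 69/0.70 = 99 | failed |
| 80% | 95% | 79 | 79/0.80 = 99 | failed |
| 80% | 96% | 86 | 86/0.80 = 108 | not failed |
| 95% | 96% | 86 | 86/0.95 = 91 | failed |
| 95% | 97% | 96 | 96/0.95 = 101 | not failed |

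Take a patient intubated on Day 2 or 3 with a set rate of 20/min (assumed), FiO2 60% and SO2 93% at 96 hours. The rate and the ratio do not fail. SpO2 then depends on how baseline was measured. The only conversion pair that the protocol gives is 93-94% on oxygen to 86-87% in ambient air:

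- Baseline also 93% on oxygen: 86-87 at both times, no fall. The patient is scored as not progressed.
- Baseline 93% in ambient air: 93 to 86-87, a fall of 6 to 7 points. Failure.
- Baseline 90% in ambient air: 90 to 86-87, a fall of 3 to 4 points. Not failed.

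Reading the 5% as relative to baseline gives the same three answers (6.5-7.5% of 93; 3.3-4.4% of 90).

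**Size.** The protocol gives neither an intubation rate nor a composite rate. With 30 evaluable per arm, one misclassified patient moves that arm's rate by 1/30 = 3.3 points, and five move it by 5/30 = 16.7 points. As an illustration, assume that the present definition yields 30% (placebo) v 15% (active), then add patients who failed by intubation only:

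| Added, placebo / active | Rates with ventilation counted | Difference |
|---|---|---|
| none | 30% v 15% | 15 points |
| 5% / 5% | 35% v 20% | 15 points |
| 10% / 5% | 40% v 20% | 20 points |
| 10% / 0% | 40% v 15% | 25 points |
| 5% / 10% | 35% v 25% | 10 points |

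The distortion can run in either direction, or cancel.

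**The case against.** The case on the other side is substantial and limits the point in several ways.

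- A reader might infer that every intubated patient is scored as a success. The documents do not support that. The SpO2 conversion turns an ordinary on-oxygen reading into a failure when baseline was near 93% in ambient air, and several plausible FiO2 and SO2 pairs fall at or below 100.
- A reader might infer that missing values revert to the non-severe entry status. Sections 7.3 to 7.6 record the respiratory parameters at baseline and on Days 1 to 3, so the last value before intubation may already be a failure. The procedure itself is deferred to a SAP that is not at hand.
- A reader might infer that a threshold crossed on Day 2 is certainly lost. Sections 8.1.1 and 11.5.1 are explicit about Day 4, but the synopsis sentence leaves room for a cumulative reading.
- Intubations stay visible elsewhere: in the secondary endpoints, in the WHO-scale comparison at each time point, and partly in the repeat of the composite at other days.
- The rate and ratio thresholds match the protocol's definition of severe distress in Section 5.1.1, and intubation depends partly on local practice across up to 11 sites.

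What remains is that the protocol itself fixes the components and their timing, and neither covers ventilation. Secondary endpoints show an imbalance but do not correct the primary estimate.

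**Conclusion.** The gap is real but of unknown size. Under Sections 8.1.1 and 11.5.1, a patient intubated between randomisation and 96 hours may be scored as not progressed if three conditions hold together: rate below 30, ratio above 100, and no converted SpO2 fall above 5%. Each such patient shifts an arm's rate by 3.3 points, and the treatment difference may move either way.

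One might go further and quote a power loss. If true progression were 40% v 20% and a quarter of progressors in each arm were masked, exact enumeration with 30 per arm at one-sided 0.025 gives 28% power instead of 39%. If half were masked, it gives 19%. These figures are hypothetical: neither the rates nor the masked share comes from the protocol, many ventilated patients would still fail, and the study is not sized on power. The argument for change is the validity of the primary estimate.

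**What to change.** In Sections 8.1.1 and 11.5.1 and in both places in the synopsis:

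1. Add as a failure event: invasive mechanical ventilation started at any time from randomisation to the 96-hour assessment, whatever the respiratory rate, SpO2 or PaO2/FiO2 then measured.
2. Derive it from the ventilation data collected for the secondary endpoints. The WHO score is unsuitable as the source: Sections 7.3 to 7.7 ask for NEWS-2 and/or WHO, so it may be absent, and it describes only the moment of the visit.
3. State that a ventilated patient is not imputed as a success from values taken before ventilation.
4. Use one timing phrase throughout, and say whether the physiological components are read at Day 4 or by Day 4. State the matching rule for the repeat analyses at other days.
5. Keep the present definition as a sensitivity analysis.

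The cost is a short amendment and no new assessment, assuming that the eCRF holds the start of ventilation precisely enough to place it before or after 96 hours. The component-wise and multi-component analyses in Section 11.5.1, which now count three non-death components, need matching edits. The composite also gains an element that depends partly on a clinician's decision and local practice. Blinding limits that, and the sensitivity analysis shows its effect.

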## 9. SECONDARY ENDPOINTS

### 9.1 EFFICACY

- All cause Death at day 40 and Overall Survival
- WHO-COVID-19 Scale
- NEWS-2 Scale
- Respiratory Rate status defined as::
  - Normal:  $< 20/\text{min}$ ,
  - Mild:  $20 \leq RR < 24/\text{min}$ ,
  - Moderate:  $24 \leq RR < 30/\text{min}$ ,
  - Severe:  $\geq 30/\text{min}$ ,
  - Death.
- Hypoxemia status defined as::
  - Normal:  $> 300 \text{ mmHg}$ ,
  - Mild:  $200 \text{ mmHg} < PaO_2/FiO_2 \leq 300 \text{ mmHg}$ ,
  - Moderate:  $100 \text{ mmHg} < PaO_2/FiO_2 \leq 200\text{mmHg}$ ,
  - Severe:  $PaO_2/FiO_2 \leq 100\text{mmHg}$ ,
  - Death.
- $SpO_2$  status defined as:
  - Normal:  $> 95\%$
  - Mild:  $93 < SpO_2 \leq 95\%$ ,
  - Moderate:  $90 < SpO_2 \leq 93\%$ ,
  - Severe:  $\leq 90\%$ ,
  - Death.
- Chest CT-Scan (or in exceptional cases, chest radiogram)
- Oxygen-free days (over the study period = 40 days),
- Need for mechanical ventilation,

- Mechanical ventilation-free days,
- Hospital-free days (over study period = 40 days),
- Clinical Recovery and Time to Clinical recovery (over study period = 40 days),
- Cure and Time-to-cure (over study period = 40 days).

## 9.2 SAFETY

- Incidence, nature and severity of Adverse Events, SAEs, SUSARs and Treatment-Emergent Adverse Events (TEAEs),
- Incidence of bleeding-related events,
- Incidence of hypersensitivity reactions,
- Changes to vital signs over the course of the study versus screening,
- Change to clinical laboratory assessments (hematology, biochemistry, urinalysis) over the course of the study versus screening,
- ECG over the course of the study versus screening.

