## 4.2 STUDY DURATION FOR THE PATIENT

For each given patient, schedule will include:

- A screening assessment upon admission to ensure of diagnosis and inclusion criteria
- At Day 1:
  - a baseline visit followed by a randomization procedure, initiation of first infusion,
  - a post-infusion evaluation at 3 hrs (+/-1hr) after the end of administration.
- At Day 2:
  - Initiation of second infusion (pending results of prior evaluation)
  - A post-infusion evaluation at 3 hrs (+/-1hr) after the end of second administration if a second administration takes place.
- At Day 3:
  - Initiation of third infusion (pending results of prior evaluation)
  - A post-infusion evaluation at 3 hrs (+/-1hr) after the end of third first administration if a third administration takes place.
- At day 4: a follow-up evaluation at 96 hrs (+/- 3 hrs), post beginning of first administration (primary end-point recording).
- At day 5: a follow-up evaluation at 120 hrs (+/-3 hrs), post beginning of first administration.
- In case, the administration is not repeated, post-infusion evaluation at 3hrs at Day 2 and Day 3, Day 4 (96 hrs), Day 5 (120 hrs) visits should take place anyway.
- A follow-up visit at Days 7 (+/-1 day), 14 (+/- 2 days) and 20 (+/-2 days),

- A 40-day (+/-3 days) post-treatment final evaluation, (End-Of- Study visit).

Additional follow-up visits, or phone calls may be required on a need basis notably in case of emerging or prolonged adverse events. Remote visits utilizing specific devices can be undertaken if it is not desirable that the patient, if discharged comes back to the institution.

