#### 5.1.1 Inclusion Criteria

1. Male or female hospitalized patients  $\geq 18$  years (i.e., at least 18 years old at the time of randomization) and  $< 80$  years, having given their written consent.
2. Having a positive RT-PCR or antigenic test for COVID-19, or with a highly positive serology AND clear symptoms of COVID-19,
3. Presenting with symptoms of COVID-19, including:
  - Cough
  - OR

- Shortness of breath or difficulty breathing  
OR at least 2 of the following
  - Fever, defined as any body temperature  $38^{\circ}\text{C}$
  - Chills
  - Repeated shaking with chills
  - Muscle pain
  - Headache
  - Sore throat
  - New loss of taste or smell
4. Presenting with signs of moderate but progressive pulmonary disease in the last 48 hours with:
- Respiratory symptoms (cough, dyspnea, etc.),
  - Uni- or bilateral ground-glass opacities, or pulmonary infiltrates on chest radiograph and/or CT scan performed within the past 96hrs,
  - Clinical and/or biological evidence of progression over the past 48hrs.
  - Progression will be assessed as follows:
    - symptom worsening: increase in the number of symptoms, and/or in the intensity of some of them  
And/or
    - worsening of respiratory condition: increase in respiratory rate and/or decrease of  $\text{PaO}_2/\text{FiO}_2$  in ambient air  
And/or
    - worsening of biological markers: CRP increase or increase of other severity/prognostic markers, and/or increase of D-Dimers
5. Presenting with a **moderate** respiratory distress defined as:
- a) At least one of the following signs associated with the onset of ARDS:
- Respiratory rate (RR)  $\geq 24/\text{min}$ ,  
OR
  - $\text{SpO}_2 \leq 93\%$  in ambient air. In case where oxygenotherapy cannot be discontinued, please refer to NEWS 2 Scale (item  $\text{SpO}_2$ , scale 2) for adequate conversion (e.g. 93-94 on  $\text{O}_2$  corresponding to 86-87 in ambient air),  
OR
  - $\text{PaO}_2/\text{FiO}_2 \leq 200\text{mmHg}$  (please refer to Appendix 3 for conversion).
- AND**
- b) NOT in a **severe** respiratory distress defined as:
- Respiratory rate (RR)  $< 30/\text{min}$ ,  
And
  - $\text{PaO}_2/\text{FiO}_2 > 100\text{mmHg}$ .

6. Presenting with signs of a pro-thrombotic status characterized by:

- a. D-Dimers  $\geq 0.5 \mu\text{g/mL}$ ,
  - b. and/or Troponin T  $> 2.5 \mu\text{g/L}$  (or by default Troponin I greater than local laboratory reference),

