## 7.3 BASELINE / RANDOMIZATION

Randomization will be performed automatically via the IxRS by the site. Detailed procedure will be described in the dedicated instruction manual. The following examination will be performed before randomization. General and specific examinations and tests that are part of the standard-of-care for Covid-19 management are not study specific and results can be used for the screening/eligibility assessment of the patients before the signature of the informed consent.

- Validation of eligibility criteria assessed during screening visit
- Vital signs (BP, Pulse); 1-time-point pharmacokinetics (baseline);
- Blood sample for Anti-glenzocimab antibodies (ADA) assessments will be collected and sent to the central laboratory;

- Soluble GPVI will be collected and sent to the central laboratory;
- Local blood sample test;
- Respiratory distress parameters:
  - Respiratory Rate (RR),
  - Oxygen saturation (SpO2),
  - PaO2/FiO2 (please refer to Appendix 3 for conversion);
- Chest CT-scan (to be repeated only if the previous one done more than 48 hrs prior to randomization);
- NEWS-2 and/or WHO scales;
- Concomitant medication;
- Recording of adverse events according to NCI-CTCAE;
- IxRS (Randomisation and Day 1 kit allocation).

The randomization visit should be performed within 24 hrs after the screening visit, once all eligibility criteria have been collected and checked.

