**11.5.2 Safety Analyses**

Usual descriptive statistics will be used and detailed in the SAP to analyze the safety parameters as follows:

- Deaths, SAEs, TEAEs and bleeding events, and of patients withdrawn because of safety concerns.
- Type, time of occurrence post dosing, frequency, seriousness, severity and relatedness of IMP emergent adverse events (TEAEs) will be analyzed. TEAEs will be analyzed according to current version of the MedDRA (Medical Dictionary for Regulatory Affairs) dictionary.
- Vital signs will be described and analyzed as needed at the various time-points across the whole study period.
- Laboratory abnormalities will be described and listed by dose level and for the placebo. Reference will be made to multiples of the upper normal limit (UNL) as defined by the laboratory’s specifications. Shift tables will be issued.
- Immunogenicity will be analyzed both in frequency (including the presence of non-clinically relevant ADA) and severity if clinically expressed, and per dose-group level.

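### Change in vital signs and blood tests is defined against screening, although both are measured again just before the first infusion (minor)

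*Protocol*

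**What the plan says.** Section 9.2 of the protocol lists as safety endpoints "Changes to vital signs over the course of the study versus screening" and "Change to clinical laboratory assessments (hematology, biochemistry, urinalysis) over the course of the study versus screening". ECG is given the same reference. The safety endpoints in the synopsis say the same.

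The schedule provides a later pre-dose measurement for two of these three groups. The baseline list in section 7.3 includes "Vital signs (BP, Pulse); 1-time-point pharmacokinetics (baseline" sample and "Local blood sample test", and the flowchart in section 7.1 marks vital signs and the local blood sample at both screening and baseline. Section 4.2 places on Day 1 "a baseline visit followed by a randomization procedure, initiation of first infusion", so the baseline values precede dosing. Section 7.3 sets the gap: "The randomization visit should be performed within 24 hrs after the screening visit".

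The safety analysis text in section 11.5.2 names no other reference. For vital signs it says only "Vital signs will be described and analyzed as needed at the various time-points across the whole study period". For laboratory values it announces shift tables without saying which visit they start from.

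**The concern.** Patients enter this trial while their disease is moving: inclusion criterion 4 in section 5.1.1 requires "Clinical and/or biological evidence of progression over the past 48hrs". Values taken at screening can be expected to differ from those taken just before the first infusion. If change is computed from screening, a within-arm summary at an early visit mixes what happened before any study treatment with what happened after it.

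An invented record shows the mechanism. Suppose haemoglobin is 13.0 g/dL at screening, 12.2 at baseline and 12.0 at the Day 1 evaluation. Change versus screening is 12.0 − 13.0 = −1.0 g/dL. Change after dosing began is 12.0 − 12.2 = −0.2 g/dL.

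What is at stake is how clearly descriptive safety tables can be read in a trial of about 30 patients per arm. The choice is also out of step with the rest of the protocol. Change on the WHO scale is taken from baseline (section 11.5.1), and treatment-emergent adverse events are anchored to the first dose (section 9.5.2). A laboratory shift between screening and baseline would thus count as change on study, while an adverse event arising in the same hours would not be treatment-emergent unless it later worsened on treatment.

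**Working it through.** The protocol states no figure here that could be reproduced. The check compares the endpoint wording with the visit schedule and then uses simple arithmetic on visit times.

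**Which measurements have a pre-infusion baseline value** (sections 7.1 to 7.3)

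| Measurement | Screening | Day 1 baseline |
|---|---|---|
| Vital signs | yes | yes |
| Local blood sample (haematology, coagulation, biochemistry) | yes | yes |
| Urinalysis | yes | no |
| 12-lead ECG | yes | no |

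So a better reference exists for vital signs and blood tests. For urinalysis and ECG, screening is the only scheduled pre-dose value.

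**Share of the change interval that precedes dosing**

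Inputs:
- Gap g from screening to baseline: at most 24 h (section 7.3).
- Infusion length: 6 h. Evaluation: 3 h after the end of each infusion. Infusions start 24 h apart (sections 4.1 and 7.4 to 7.6).
- Assumption: the first infusion starts at the baseline visit.

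Hours t from the start of the first infusion to each evaluation:
- Day 1: 6 + 3 = 9
- Day 2: 24 + 9 = 33
- Day 3: 48 + 9 = 57
- Day 4: 96
- Day 7: 7 × 24 = 168
- Day 40: 40 × 24 = 960

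Pre-dose share = g / (g + t).

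| Evaluation | g = 24 h (limit) | g = 12 h |
|---|---|---|
| Day 1 | 24/33 = 73% | 12/21 = 57% |
| Day 2 | 24/57 = 42% | 12/45 = 27% |
| Day 3 | 24/81 = 30% | 12/69 = 17% |
| Day 4 (96 h) | 24/120 = 20% | 12/108 = 11% |
| Day 7 | 24/192 = 13% | 12/180 = 7% |
| Day 40 | 24/984 = 2% | 12/972 = 1% |

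With the baseline visit as reference, the share is about 0 at every evaluation for vital signs and blood tests.

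The 24 h limit runs from screening to the randomization visit. Section 7.3 also allows standard-of-care results obtained before consent to serve for screening, so for some values the gap could be longer.

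**The case against.** The strongest reply is that section 9.2 is a list of endpoints and not a derivation rule. Section 11.5.2 leaves the details of the safety statistics to the SAP, where the operational definition of baseline usually sits. Screening is also the only pre-dose visit that has all the listed assessments, so it is a uniform reference. Safety attribution runs mainly through adverse events, and clinically relevant laboratory and vital-sign abnormalities are recorded as such. Section 4.5 has the safety board review adverse events and laboratory abnormalities by arm, and it does not mention change from screening.

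Much of this stands, and it limits the point. A reader might infer four stronger things, none of which the protocol supports:

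- *That pre-dose change is counted as change on study drug.* The text speaks of change over the course of the study. It does not say on treatment or since the first dose.
- *That the pre-dose value is never used.* Section 11.5.2 describes vital signs across all time-points, which can include baseline, and it states no starting visit for the shift tables.
- *That the treatment comparison is biased.* Screening precedes a 1:1 randomization against placebo, so pre-dose drift is expected to be equal in the two arms.
- *That 73% of an observed change is spurious.* The figure is a share of hours, at the maximum gap and the earliest evaluation. The documents hold no data on how far values move between screening and baseline.

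The reply does not remove the point. The protocol does not leave the reference open: it names screening in 9.2 and in the synopsis, and nothing later replaces it. If the SAP, which is not available here, uses a pre-infusion baseline, the two documents would disagree. Uniformity is a weak reason to pass over a closer measurement that is already scheduled.

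**Conclusion.** The point holds in a limited form and is minor. For vital signs and blood tests, the protocol chooses the earlier of two scheduled pre-dose values as the reference, in patients selected for recent progression. Descriptive within-arm changes, and shift tables if they are built on that reference, would include pre-dose change. The effect is confined mainly to the first three evaluations, where pre-dose time is up to 73%, 42% and 30% of the interval, and it fades to about 2% at Day 40. These figures assume the full 24 h gap and an infusion starting at the baseline visit; a 12 h gap gives 57%, 27% and 17%.

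The comparison between arms remains unbiased. A more distant reference may add noise to change scores, but the documents give no variances or correlations from which to size it. The primary endpoint is unaffected.

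**What to change.** In section 9.2 and in the safety endpoints of the synopsis, define the reference for change as the last value before the start of the first infusion. For vital signs and blood tests this is the baseline visit. Keep screening as the reference only where no baseline measurement is scheduled (ECG, urinalysis) or where the baseline value is missing. State the same reference for the shift tables in section 11.5.2, and make sure the SAP agrees.

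The cost is one sentence in each place. The data are already collected, and no visit, procedure or aspect of patient care changes.
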